## Abstract

**Background:**

In 2014, the national population-based colorectal cancer (CRC) screening program was implemented in the Netherlands. Biennial fecal immunochemical testing (FIT) for hemoglobin (Hb) is used at a cut-off of 47 µg Hb per gram feces. The CRC screening program successfully started, with high participation rates and yield of screening. Now that the program has reached a steady state, there is potential to further optimize the program. Previous studies showed that prior fecal Hb (f-Hb) concentrations just below the FIT cut-off are associated with a higher risk for detection of advanced neoplasia (AN) at subsequent screening rounds. We aim to achieve a better balance between the harms and benefits of CRC screening by offering participants tailored invitation intervals based on prior f-Hb concentrations after negative FIT.

**Methods:**

This mixed-methods study will be performed within the Dutch national CRC screening program and will consist of: (1) a randomized controlled trial (RCT), (2) focus group studies, and (3) decision modelling. The primary outcome is the yield of AN per screened individual in personalized screening vs. uniform screening. Secondary outcomes are perspectives on, acceptability of and adherence to personalized screening, as well as long-term outcomes of personalized vs. uniform screening. The RCT will include 20,000 participants of the Dutch CRC screening program; 10,000 in the intervention and 10,000 in the control arm. The intervention arm will receive a personalized screening interval based on the prior f-Hb concentration (1, 2 or 3 years). The control arm will receive a screening interval according to current practice (2 years). The focus group studies are designed to understand individuals’ perspectives on and acceptability of personalized CRC screening. Results of the RCT will be incorporated into the MISCAN-Colon model to determine long-term benefits, harms, and costs of personalized vs. uniform CRC screening.

**Discussion:**

The aim of this study is to evaluate the yield, feasibility, acceptability and (cost-) effectiveness of personalized CRC screening through tailored invitation intervals based on prior f-Hb concentrations. This knowledge may be of guidance for health policy makers and may provide evidence for implementing personalized CRC screening in The Netherlands and/or other countries using FIT as screening modality.

*Trial registration:* ClinicalTrials.gov, NCT05423886, June 21, 2022, https://clinicaltrials.gov/ct2/show/NCT05423886

**Supplementary Information:**

The online version contains supplementary material available at 10.1186/s12876-023-02670-1.

## Background

In 2014, a national population-based colorectal cancer (CRC) screening program was implemented in the Netherlands. Biennial fecal immunochemical testing (FIT) for hemoglobin is used at a cut-off of 47 µg (µg) hemoglobin (Hb)/g (gram) feces. The CRC screening program successfully started, with high participation rates and yield of screening resulting in a decrease in overall and advanced-stage CRC incidence [1–3]. Now that the program has reached a steady state, there is potential to further optimize the program.

Every year, about 2.2 million people are invited to participate in the Dutch CRC screening program. The participation rate is about 72% [4]. About 4.5% of participants has a positive FIT, meaning they have a fecal hemoglobin (f-Hb) concentration above the pre-set FIT cut-off [4]. Of these participants, about 85% undergo a colonoscopy, with around 40% of these people having a relevant finding (6% CRC and 36% advanced adenoma (AA)) [4]. This implies that about 98% of participants in CRC screening do not experience any benefit from screening; 95.5% of participants because they have a negative FIT and 2.7% because they have a positive FIT without relevant findings at colonoscopy.

Ideally, screening should be offered primarily to those who would benefit most, that is, those who are at high risk of the disease. Personalized screening has been discussed for a long time (about 25 years) [5]. To date, however, such an approach has not taken off, due to the limited predictive power of a number of known risk factors [6]. A risk model that combined genetic information with lifestyle factors, family history and sex had a discriminatory power of 63% for predicting CRC risk [10].

There is increasing evidence that f-Hb concentration is a good predictor of future diagnosis of advanced neoplasia (AN) (Table 1). Models incorporating f-Hb concentrations could reach a discriminatory power of about 80% [6–10]. The major advantage of this predictive factor is that the f-Hb concentration is automatically obtained within FIT-based CRC screening programs and thus is readily available information. The likelihood that the integration of tailored invitation intervals based on prior f-Hb concentration after negative FIT lowers the participation rate is therefore smaller than if another (not automatically obtained) risk factor would be used to personalize CRC screening. Sex and age are also automatically registered, but their predictive value is much lower than the f-Hb concentration (odds ratios for AN: 1.6 (male sex) and 0.9–1.1 (increasing age) vs. 2.5–21.8 (increasing f-Hb concentrations), respectively [7]). In addition, a strong association was observed between the measured f-Hb concentration in participants with a negative FIT and the risk of developing interval CRC in the Dutch CRC screening program [11]. Interval CRC is defined as CRC diagnosed after a negative FIT and before invitation to the next screening round [12]. Participants in the category with an f-Hb concentration just below the FIT cut-off (15–46.9 µg Hb/g feces) are 13 times more likely to develop an interval CRC compared to participants with an unmeasurable f-Hb concentration (0 µg Hb/g feces) [*personal communication*].

**Table 1 Tab1:** Risk of AN and/or CRC in subsequent screening rounds in high-risk individuals compared to low-risk individuals

Program	FIT cut-off	Comparison high- vs. low-risk individuals	Main outcome	Risk of AN and/or CRC in subsequent round
Dutch pilot studies ^14^	10 µg Hb/g feces	8–10 µg Hb/g feces vs. 0 µg Hb/g feces	AN	Hazard ratio: 8
Flemish CRC screening program^15^	15 µg Hb/g feces	Males aged 74 and 200 µg Hb/g feces vs. females aged 56 and 15 µg Hb/g feces	CRC	Odds ratio: 15
Dutch CRC screening program^16^	47 µg Hb/g feces	15–46.9 µg Hb/g feces vs. 0 µg Hb/g feces	AN	Odds ratio: 23
Scottish CRC screening program^17^	80 µg Hb/g feces	60.0–79.9 µg Hb/g feces vs. 0.0–19.9 µg Hb/g feces	AN	Odds ratio: 38

*CRC* colorectal cancer, *FIT* fecal immunochemical testing, *µg Hb/g* microgram hemoglobin per gram, *AN* advanced neoplasia

Almost half of all interval CRCs occur in a small group of participants (3.5%) with an f-Hb concentration between 15 and 46.9 µg Hb/g feces [13]. Two-thirds of these cancers occur in the second year after screening [13]. This means that one-third of interval CRCs could potentially have been prevented by inviting only 3.5% of participants to screening one year earlier. Based on more recent data, we expect around 85% of participants to have an f-Hb concentration of 0 µg Hb/g feces and thus to be at lowest risk of developing an interval CRC. If the interval between invitations for this group would be extended by one year, this would represent a 40% reduction in the screening burden for the population as a whole.

Now that the FIT-based CRC screening program has been fully rolled out in the Netherlands, has high participation rates and shows favorable results, there is potential for further optimization of the CRC screening program. We designed a mixed-methods study consisting of: (1) a parallel group, two-arm, superiority randomized controlled trial (RCT), (2) focus group studies, and (3) decision modelling. The aim of this mixed-methods study is to identify the yield and (cost-) effectiveness of personalized CRC screening, whether it could be feasible within population-based CRC screening programs, and whether the population is able to understand and accept it.

## Methods/design

### Objectives

The aim of this study is to evaluate the yield, feasibility, acceptability and (cost-) effectiveness of personalized CRC screening through tailored invitation intervals based on prior f-Hb concentrations. Table 2 describes the aims, outcomes, and designated components of the study.

**Table 2 Tab2:** Aims, outcomes and designated components of the PERFECT-FIT study

Aim	Outcome	Component of the mixed-methods study
Yield	Detection rate	RCT
Effectiveness	Detection of AN	RCT
	Cost-effectiveness	Decision modeling
	Long-term outcomes (incidence & mortality)	Decision modeling
Feasibility	Participation rate	RCT
	Information needs in personalized screening	Focus group I
Acceptability	Information needs in personalized screening	Focus group I
	Perspectives on personalized screening	Focus groups II and III

*RCT* randomized controlled trial, *AN* advanced neoplasia, *PERFECT-FIT*
personalized colorectal cancer screening: effectiveness of tailored intervals based on prior f-Hb concentration in a FIT-based colorectal cancer screening program

The primary objective of this study is to compare the yield (detection rate; DR) of AN per participant of personalized CRC screening (intervention arm) to uniform biennial CRC screening (control arm). AN is defined as AA or CRC. AA is defined as an adenoma with high grade dysplasia, and/or > 25% villous component, and/or ≥ 10 mm diameter. The DR is defined as the number of individuals with AN per 1000 screened individuals. Currently, advanced serrated polyps (ASPs) are not yet considered as relevant findings of the Dutch FIT-based screening program. However, this could change in the near future, due to new insights into the relevance of the serrated pathway in carcinogenesis. If ASPs are added to the relevant findings of the national CRC screening program, we will also evaluate the yield of the RCT with an updated definition of AN (AA + ASP + CRC).

The secondary objectives are to determine perspectives on, acceptability of and adherence to personalized CRC screening. Furthermore, we aim to evaluate the (cost-) effectiveness of personalized CRC screening compared to the current screening strategy.

This study was approved by the Health Council and fell under the Population Research Act. It was registered at Clinical Trials (NCT05423886) and started on October 14th, 2022. Additional file 1: Table 1 contains all items from the World Health Organization Trial Registration Data Set.

### Study design

This study is a mixed-methods study consisting of three parts: (1) a parallel group, two-arm, superiority randomized controlled trial (RCT), (2) focus group studies, and (3) decision modelling. This study will be performed over a time period of three years (Fig. 1). A concise time schedule can be found in Additional file 1: Table 2.

**Fig. 1 Fig1:**
[figure not shown]
Time schedule of the PERFECT-FIT study. *FIT* fecal immunochemical testing, *RCT* randomized controlled trial, *PERFECT-FIT*
personalized colorectal cancer screening: effectiveness of tailored intervals based on prior f-Hb concentration in a FIT-based colorectal cancer screening program

## RCT

### Outcomes

We will conduct a prospective, parallel group, two-arm, superiority RCT within the Dutch national, population-based CRC screening program to evaluate the yield of personalized CRC screening by determining the DR of AN (and potentially the updated definition of AN including ASPs) in the intervention and control arm. Furthermore, feasibility will be determined by comparing participation rates between the intervention and control arm.

### Study procedures

The design and logistics of this proposed study will be embedded in the nationwide FIT-based CRC screening program. Screening-eligible individuals with a prior negative FIT (irrespective of screening round) within the Dutch CRC screening program will be included. These individuals will have had a negative FIT ≤ 8 months before inclusion and will have a maximum age of 72, in order for them to undergo at least one more round of screening after participating in the RCT. Individuals will be randomly selected by the CRC screening authority (Bevolkingsonderzoek-Nederland; BVO-NL) from the Mid-West area in the Netherlands.

Individuals who meet the inclusion criteria will be approached by the screening organization (BVO-NL) to participate in the study. Information about the trial will be provided to participants through an information leaflet. Participants will receive the information leaflet by mail, including an informed consent form and a return envelope. General practitioners in the relevant region will receive additional information about the RCT. All individuals will be asked to give informed consent and participate in scientific research, both in the intervention and control group. If individuals choose not to participate, no reminder will be sent and they will receive a standard invitation for screening conform current practice.

After providing informed consent, participants will be randomized 1:1 to the control or intervention arm by block randomization according to a computer-generated randomization schedule using permuted blocks. Block sizes will not be disclosed for privacy purposes. Participants will be randomized using R version 4.0.2. Concealment of allocation will be ensured by data transmission through a digital research environment. All participants will be informed whether they have been randomized to the control or intervention arm and will receive a notification letter regarding their invitation interval. Participants in the control arm will receive an invitation to perform FIT at the regular invitation interval, after two years of their prior negative FIT. Individuals in the intervention arm receive information on their prior f-Hb concentration and their corresponding invitation intervals (Fig. 2). They are notified on whether they had little (> 15–46.9 µg Hb/g feces), very little (> 0–15 µg Hb/g feces), or no blood in their stool (0 µg Hb/g feces). They will receive an invitation to perform FIT at the designated invitation interval corresponding with their f-Hb concentration (little blood: 1 year; very little blood: 2 years; no blood: 3 years, Fig. 2).

**Fig. 2 Fig2:**
[figure not shown]
Randomization of participants in the RCT. *µg Hb/g* microgram hemoglobin per gram, *RCT* randomized controlled trial

If an individual does not respond to the invitation, a reminder will be sent after six weeks, conform current practice. Study participants will receive the result of the FIT (negative or positive) according to current practice and in case of a positive FIT also an invitation for an intake appointment for a colonoscopy. The existing IT infrastructure of the CRC screening program, ScreenIT, will be used and adjusted to facilitate allocating personalized invitation intervals within the screening process.

After all participants have performed their FIT within the study, they return to the regular CRC screening program and will again be invited after two years to perform FIT if appropriate.

### Sample size calculation

The power calculation is based on the main endpoint of this study: the yield (DR) of AN (CRC + AA) in the control arm versus the intervention arm. To detect a difference in DR of 0.5% between the intervention and control arm, 20,000 FIT participants are needed. With 20,000 inclusions, we have sufficient power to demonstrate a difference in detection rate of 2.2% in the intervention arm vs. 1.7% in the control arm. Given the high adherence rates of previous participants to subsequent screenings (93%), we conservatively assume that 40% of the invited population is willing to participate in this trial. This means that 50,000 individuals need to be invited to this RCT to demonstrate superiority in yield of risk-based screening. However, if participation rates are lower than expected, more invitations will be sent out until we have reached the total of 20,000 inclusions.

### Data management

All data will be entered electronically by scanning a barcode. The original informed consent forms will be entered into the system and kept on file at the study site. Files are stored in numerical order in a safe, accessible location. Participant records will be retained for at least 15 years after study completion. All reports, data collection, trial and administrative forms will be identified only by an encoded ID number to ensure participant confidentiality. All records with names or other personal identifying information, such as a locator form or informed consent form, are stored separately from study records with ID numbers. All local databases will be protected with password-protected access systems. Forms, spreadsheets, logbooks, and other lists that link participant IDs to other identifying information are stored in a separate locked file in a restricted area. The datasets generated and/or analyzed in this study are not publicly available, but are available on request from BVO-NL. A data transfer agreement will be drawn up in the event of data sharing between BVO-NL and the PERFECT-FIT study team. Data Integrity is enforced through a Data Management Plan; data is owned by BVO-NL and is protected according to the General Data Protection Regulation and other applicable guidelines.

### Study procedures: logistics

A study invitation letter will be sent to a selection of screen-eligible individuals who had a negative FIT ≤ 8 months earlier and are still eligible for a subsequent screening round. Invitation letters are sent out in batches of 10,000 invitations. The study invitation will include an information letter and an informed consent form (for the RCT as well as focus groups). Invitees who wish to participate in the study send the informed consent form to the investigators.Informed consent will be returned in a prepaid, pre-addressed return envelope that is sent to the researchers. The barcode on the informed consent will be scanned by one researcher and will be checked by a second researcher.All patients who consent for participation and meet the inclusion criteria will be randomized into either the control or intervention arm by using 1:1 block randomization. No blinding will be performed, as both the investigators and the participants will be informed of the assigned invitation interval. Information on informed consent and randomization of study participants is stored in the eCRF CASTOR.BVO-NL supplies information on f-Hb concentrations of participants that gave consent to participate in the RCT. The researchers assign a screening interval to the participant based on their assigned group and, if applicable, prior f-Hb concentration.Study participants will receive a confirmation letter, stating when the client will be invited again according to the study design (intervention arm: 1, 2 or 3 years and control arm: 2 years).Study participants will receive their FIT within the RCT and will perform the FIT conform the regular screening process.During the study, only the invitation interval of study participants in the intervention arm (1 and 3 years) will be changed. Study participants will receive the regular CRC screening program outcome letter (negative FIT at a cut-off of 47 µg Hb/g feces or positive FIT with an invitation for a follow-up colonoscopy). After participating in the study, all study participants will return to the regular screening program and will be invited to participate in CRC screening two years after the previous invitation date, unless the participant had a positive FIT and was referred for colonoscopy.Individuals returning their consent forms too late (> 3 weeks after receiving their information leaflet and informed consent form) will be excluded from the study and thus follow the regular screening process.A monitoring report provided by BVO-NL will be used to track the progress of the study (including invitations sent and participation rate). If needed, the number of invitations sent will be expanded to reach 20,000 inclusions.At three time points during the study (i.e. 1, 2 and 3 years after inclusion), researchers will receive a report of results from participants who have given informed consent for the study. From study invitees who did not participate in the study (no informed consent), the researchers will receive a report with aggregated/anonymous data (i.e., information on age, sex and f-Hb concentration) to be able to assess generalizability of the results to the entire population.Upon completion of the study, BVO-NL will verify that the study invitees will receive another invitation to the CRC screening program, two years after performing their FIT within the study, according to current practice (unless the participant had a positive FIT).In case participants have logistical questions about the study or the regular CRC screening program, they can visit the study website or ask them by e-mail. There will also be a telephone line available for questions, which will be answered by the researchers of the Erasmus MC.

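### If the month-36 report is the last outcome extract, the 3-year group has 0–8 months from invitation to result and controls have 12–20

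*Protocol article*

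**What the plan says.** Five statements in the protocol article set the calendar.

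- Study procedures, on eligibility: "These individuals will have had a negative FIT ≤ 8 months before inclusion".
- Study procedures, on the control arm: the invitation comes "at the regular invitation interval, after two years of their prior negative FIT".
- Study procedures, on the intervention arm: "little blood: 1 year; very little blood: 2 years; no blood: 3 years". The article does not say from which date these intervals run.
- Study procedures: logistics, on outcome data: "At three time points during the study (i.e. 1, 2 and 3 years after inclusion), researchers will receive a report of results from participants". No later report is described.
- Study design, on total length: "This study will be performed over a time period of three years".

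Two more statements bear on the size of the problem. The Background gives the expected share on the 3-year interval: "we expect around 85% of participants to have an f-Hb concentration of 0 µg Hb/g feces". Study procedures (text after Fig. 2) says of non-responders that "a reminder will be sent after six weeks", and that a positive FIT leads to an intake appointment for colonoscopy.

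The primary outcome (Objectives) is the number of people with AN per 1000 screened. Feasibility (RCT, Outcomes) is judged by comparing participation between arms.

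**The concern.** Invitations are dated from the prior FIT, at least in the control arm, while outcome reports are dated from inclusion. The longest invitation interval and the last listed report are both three years, so the two nearly coincide for most of the intervention arm. Controls, invited a year earlier, have had at least a year to return the kit, be referred and be diagnosed.

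If the analysis uses the month-36 report, completeness of outcome depends on the arm. That affects the primary comparison and the participation comparison. It also affects the yield at the 3-year interval, which the Cost-effectiveness analysis section uses to validate MISCAN-Colon.

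The three-year duration raises the same difficulty separately, since recruitment runs in batches and each 3-year interval has to fit after inclusion.

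**Working it through.** The plan states no follow-up window after the study invitation, so there is no figure of its own to reproduce. The windows below follow from its dates.

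**1. Time from invitation to the month-36 report.** Let f be the months from prior FIT to inclusion, 0 to 8. An interval of k years dated from the prior FIT gives an invitation at 12k − f months after inclusion. The time left is 36 − (12k − f).

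| Group | Invitation (months after inclusion) | Time left at month 36 |
|---|---|---|
| Control, 2 years | 16–24 | 12–20 months |
| Intervention, 1 year | 4–12 | 24–32 months |
| Intervention, 2 years | 16–24 | 12–20 months |
| Intervention, 3 years | 28–36 | 0–8 months |

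If the 3-year interval instead ran from inclusion, the invitation would fall at month 36 and the time left would be 0.

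**2. Share of the 3-year group not yet complete.** Assumption: f is uniform over 0–8 months.

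- Six weeks is 42/30.4 = 1.38 months. 1.38/8 = 17% of the 3-year group would not have reached the reminder date, or 0.85 × 17% ≈ 15% of the arm.
- The time from invitation to diagnosis is not in the documents. At an assumed 2 months, 2/8 = 25% of the group is incomplete; at 4 months, 4/8 = 50%. As a share of the arm this is 0.85 × 25% = 21% to 0.85 × 50% = 43%.
- Controls have at least 12 months, so none are incomplete under these lags.

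**3. The three-year duration.** Someone included s months after study start receives the 3-year invitation at month s + 36 − f. That is inside 36 months only if s < f, and f is at most 8. For example, s = 6 and f = 4 gives month 38, before any time for FIT return or colonoscopy.

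**4. Effect on the detection rate (DR) per screened person.** Let w be the 3-year group's share of AN, F the months from invitation to FIT return and L the months from invitation to diagnosis. If everyone is eventually screened and the complete-data DR is the planned 2.2%, the DR seen at month 36 is

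2.2% × (1 − w × L/8) / (0.15 + 0.85 × (1 − F/8)).

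For w, take strata of 85%, 11.5% (the remainder) and 3.5% (Background). Use the Table 1 odds ratio of 23 for the top stratum, and assume 2.5 to 10 for the middle one. Solving for an overall 1.7% gives w of about 0.32 to 0.47. F and L are assumptions.

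| F (months) | L (months) | Observed DR |
|---|---|---|
| 1 | 3 | 2.03–2.17% |
| 1.5 | 3 | 2.15–2.30% |
| 1.5 | 4 | 2.00–2.20% |
| 2 | 6 | 1.80–2.12% |

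Worked case, F = 1.5, L = 3, w = 0.472: 2.2 × (1 − 0.472 × 0.375) = 1.81, the denominator is 0.15 + 0.85 × 0.8125 = 0.841, and 1.81/0.841 = 2.15%. With w = 0.322 the same lags give 1.93/0.841 = 2.30%, above the true 2.2%.

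Participation moves one way only. At F = 1.5 months, 0.85 × 1.5/8 = 16% of the arm counts as not yet screened although still within its return time.

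**The case against.** **The final cut is not stated.** The article never calls the month-36 report the final extract, a database lock or the basis of the primary analysis. Elsewhere it describes the end of study participation by FITs performed. The time schedule (Fig. 1 and Additional file 1) is not shown, and data-cut rules are often left to other documents. This stands as a limit on the claim. Still, the article lists exactly three reports, gives a three-year duration and mentions nothing later, so following the visible text produces the unequal windows.

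**The report dates may be nominal.** Inclusion could mean a batch, or the close of recruitment, rather than each person. If it meant close of recruitment, someone included r months earlier would have f + r months left. The last people recruited would still have only 0–8 months, and the study would exceed three years from its start. At any common extraction date the 3-year group has 12 months less than controls with the same f and r.

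**The problem does not cover the whole arm.** This is correct. The 1- and 2-year strata have at least as much time as controls, and 3-year participants with f near 8 months may be complete.

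**A reader might infer that the DR is biased against personalised screening.** Missing AN in one arm suggests it. If everyone stayed in the denominator, a 3-month diagnosis lag would lower 2.2% to 1.81–1.94%. However, the outcome is defined per screened person, so low-risk people who have not returned a FIT also leave the denominator. The table in the working shows results on both sides of 2.2%. The documents support neither a fixed direction nor a single size for the DR bias.

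**Conclusion.** The concern holds in limited form. The windows are exact arithmetic from the article's dates, given that the 3-year interval starts at the prior FIT: 0–8 months for about 85% of the intervention arm against 12–20 months for controls. Starting it at inclusion makes the window 0.

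Under uniform f, about 17% of the 3-year group would not have reached the reminder date. With an assumed 2–4 months to diagnosis, 25–50% of that group would be incomplete, against no controls.

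If month 36 is the last extract, which the visible text implies but does not state, measured participation is too low and AN counts are incomplete, both in the intervention arm only. The DR per screened person is then biased with uncertain sign. A bias of unknown sign in a superiority comparison still has to be removed before the primary analysis.

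Separately, the three-year duration cannot accommodate the 3-year interval for anyone included later after study start than the time since their prior FIT.

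**What to change.** 1. Reconcile the report timing and the three-year duration with the 3-year interval, and state the date from which each interval runs.
2. For the primary and participation analyses, define the outcome extract relative to each person's scheduled study invitation. Use the same window in both arms, long enough for FIT return, colonoscopy and histology.
3. Run the primary analysis only after the last 3-year invitee has completed that window.
4. Restate the study duration accordingly.

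The length of the window is for the sponsor to set from the programme's own turnaround times; what matters is that it is equal and sufficient. The invitation intervals themselves need not change. The cost is one later data extract and a later final analysis, with no extra participants or procedures.
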